#### Secondary outcomes

For the secondary outcomes PCI, CABG, HF symptoms and NYHA class, chi-square tests will be used to compare the advanced and standard imaging technologies; logistic regression analysis will be used for adjusting any pertinent baseline differences identified. For the secondary outcomes LVEF, MLHFQ and EQ5D, analysis of variance will be used to compare trends over time between the advanced and standard technologies. Analysis of covariance will be used for adjusting any pertinent baseline differences identified.

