#### Secondary objectives

To compare the effect of *HF imaging strategies* on:

1. The incidence of revascularization procedures (percutaneous coronary intervention {PCI}, CABG).

2. LVEF,

3. HF symptoms and New York Heart Association Functional Class (NYHA) class.

4. QOL (Minnesota Living with Heart Failure questionnaire (MLHFQ), the EQ5D).

5. Health economics. Costs will be estimated through regression analysis and cost effectiveness will be assessed through decision modeling.

6. The safety of imaging tests measured by cumulative radiation, adverse reactions to imaging contrast agents and stress testing agents will also be determined.

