### Sample size

For the sample size determination, the estimated occurrence over one year of the composite clinical endpoint of cardiac death, MI, resuscitated cardiac arrest and cardiac re-hospitalization (WHF, ACS, arrhythmia) for PET is 27% and for standard care is 40%, based on the Ottawa-FIVE substudy [28] of the PARR-2 [27] study in which the composite event rates were 19% and 41%, respectively. These estimates were considered reasonable as it reflects the outcome rates that may be achievable at a facility with expertise and access to FDG PET imaging. There are no similar data upon which to draw an estimate for CMR. Considering the Schinkel *et al*. publication [38], which noted sensitivity of CMR to be between PET and standard care modalities and based on expert consensus from our IMAGE-HF workshop (16 December 2008 in Toronto, Canada), we estimate the event rate for CMR directed care would lie between the above values at 34%. Hence, an overall rate for the alternative (PET, CMR) modalities would be approximately 30%. The rates are considered conservative since the mean duration of follow-up will be 2 years, whereas the PARR-2 study was 1 year.

For the primary hypothesis, using the two-sided log-rank test for comparing advanced (PET + CMR) versus standard modalities with a 2:1 patient allocation, a sample size of 495 patients (of which 330 are allocated to the advance modality and 165 are allocated to the standard modality) would be needed in order to detect a difference after 1 year in the composite clinical endpoint of 30% for the advanced modalities (PET, CMR) compared to 40% for standard care modalities (SPECT). This is calculated with a level of significance of 0.05 and power of 80%, and assuming a uniform accrual of patients over the 2.5 year recruitment period, a 1 year minimum follow-up period and a 10% loss from each study group. The difference of 10% was considered to be a minimal clinically important difference based on a consensus of the IMAGE-HF investigators.

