#### Secondary analysis (PET versus CMR)

For the secondary analysis, comparing the PET and CMR modalities, potential confounding variables of the relationship between the imaging technologies and the primary endpoint will be assessed. In particular, propensity scores based on patient factors (for example, in/outpatient, NYHA class, HF duration, diabetes, atrial fibrillation) and site factors (for example, time-to-imaging, time-to-therapy) will be used in the analysis if necessary to adjust for potential differences between PET and CMR. A Cox proportional hazard models will be used to assess the occurrence of the endpoints between the imaging technologies (the model will include a group indicator variable) adjusting for any pertinent baseline differences identified. The proportional hazards assumption underlying the Cox model will be assessed. The secondary outcomes will be analyzed in a similar fashion.

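### Chi-square for NYHA class discards its ordering and costs about 15 points of power; PCI and CABG incidence needs a defined time horizon, mainly where registry patients are compared

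*Protocol article*

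**What the plan says.** The Secondary outcomes section of the protocol article fixes the test: "For the secondary outcomes PCI, CABG, HF symptoms and NYHA class, chi-square tests will be used to compare the advanced and standard imaging technologies". For adjustment, "logistic regression analysis will be used for adjusting any pertinent baseline differences identified". It names no time point for these outcomes, no use of follow-up time and no ordinal method.

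The first item under Secondary objectives is "The incidence of revascularization procedures (percutaneous coronary intervention {PCI}, CABG"), again without a time window.

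For PET against CMR, the section on that secondary analysis describes propensity scores and a Cox model and closes with "The secondary outcomes will be analyzed in a similar fashion".

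Follow-up length comes from the Sample size section, "assuming a uniform accrual of patients over the 2.5 year recruitment period, a 1 year minimum follow-up period", which implies about 1 to 3.5 years per patient. The patient assessment schedule (Table 2) collects clinical data at baseline and 12 months.

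**The concern.** NYHA class runs from I to IV, and the secondary hypothesis is directional: better symptom reduction with advanced imaging. A Pearson chi-square across classes gives the same answer however the classes are ordered, so it spreads its power over patterns nobody expects. The baseline class enters only through the logistic model, and then only if a pertinent difference is noticed.

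Revascularisation is the route by which imaging is meant to change outcome, so its comparison will be used to interpret the primary result. A patient followed for 1 year without a procedure and one followed for 3.5 years without a procedure count the same in a crude proportion. The primary composite, under the same staggered follow-up, is analysed as time to event. If two groups are followed for different lengths of time, crude proportions differ even when procedure rates do not. Randomisation protects against that; a registry does not.

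**Working it through.** **The plan's own figure.** No power is stated for the chi-square comparisons. The arm sizes come from the primary calculation, a two-sided log-rank test at 2:1, which arrives at "a sample size of 495 patients (of which 330 are allocated to the advance modality and 165 are allocated to the standard modality"). Its target, with alpha 0.05, power 80% and 10% loss, is a 1-year event rate of 30% with advanced imaging against 40% with SPECT.

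- Hazards: −ln(0.60) = 0.511 and −ln(0.70) = 0.357 per year; ratio 0.698.
- Event probability with 2.5 years' uniform accrual and 1 year minimum follow-up: 0.661 standard, 0.537 advanced.
- Difference-in-hazards (Lachin-Foulkes) formula at 2:1: 449 patients; 449/0.9 = 499, against the stated 495.

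The figure reproduces within 1%, so the arm sizes and the 1 to 3.5 year follow-up are a sound base.

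**NYHA class at 12 months.** Inputs: 330 × 0.9 = 297 and 165 × 0.9 = 148.5, taken as 149. The SPECT distribution 20/40/30/10% is an assumption. The advanced arm is obtained by multiplying each cumulative odds by the odds ratio (OR); OR 1.5 gives 27.3/42.0/23.9/6.9%. Power at two-sided 0.05, 4,000 simulated trials per case:

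- OR 1.0: chi-square (3 df) 4.9%, Wilcoxon 4.8%; both hold their level.
- OR 1.5: 45% v 61%.
- OR 1.6: 57% v 71%.
- OR 1.7: 67% v 82%.

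Repeat runs moved these by up to about 3 points; the gap stayed at about 14 to 17 points. Splitting the scale into two categories does not recover it: about 51% and 70% at odds ratios 1.5 and 1.7. The Wilcoxon test stands in for an unadjusted proportional-odds model. Any further gain from baseline NYHA is not counted.

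**PCI and CABG, randomised arms.** Assumed: 330 v 165 patients, follow-up uniform on 1 to 3.5 years, death 10% per year in both arms.

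- No effect: chi-square rejects 4.3% (constant procedure hazard) and 5.1% (procedures clustered early), so it is valid.
- 20% v 30% per year: power 85% chi-square, 88% Gray-type test, 90% log-rank.
- 14% v 20% per year: 58%, 60%, 62%.
- Early procedures (mean 3 months), 30% v 42%: 73%, 73%, 74%.

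**Death before a procedure.** With equal procedure hazards and death at 10% v 20% per year, chi-square rejects 12.5%, the Gray-type test 11.6% and the cause-specific log-rank 5.4%. The crude proportion and cumulative incidence behave almost alike; the cause-specific test addresses a different question.

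**Comparisons that include registry patients.** Suppose follow-up is 1 to 3.5 years in one group and 1 to 3 in the other, with the same procedure hazard. The expected crude proportion is the average over follow-up times u of h/(h+m) × [1 − exp(−(h+m)u)]. With h = −ln(0.80) = 0.223 and m = −ln(0.90) = 0.105 this is 34.6% v 32.1%. At 548 per group:

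z shift = 0.025 / √(0.3335 × 0.6665 × 2/548) = 0.025/0.0285 = 0.88

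Rejection under no effect = Φ(−1.96 + 0.88) + Φ(−1.96 − 0.88) ≈ 14%.

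Simulation gave 11% to 15% for procedure rates of 10% to 30% per year, and 30% to 54% if the second group had 1 to 2.5 years. Log-rank stayed near 5%. For 1,096 advanced patients (registry included) at 1 to 3.5 years against 165 standard, chi-square rejected 9.5% with 1 to 3 years in the standard group and 12.3% with 1.5 to 3.5.

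**The case against.** A reader might infer that chi-square distorts the main revascularisation comparison. The article does not support that. Staggered entry gives both randomised arms the same follow-up distribution, the test holds its level, and the power lost is 0 to 5 points. It is about 1 point if procedures follow soon after imaging, which is plausible because the management plan is recorded within 3 months of the scan.

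A reader might also infer that chi-square mishandles death. It counts a patient who dies first as having had no procedure, much as cumulative incidence does.

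For PET against CMR, two things are uncertain. "The secondary outcomes will be analyzed in a similar fashion" may refer to the Cox and propensity methods just before it rather than to the chi-square tests. And nowhere does the article say that follow-up differs between groups; the Registry section applies the same evaluation to registry patients. The bias is therefore conditional.

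A fixed 12-month reading of the chi-square tests is possible, every patient having at least 1 year of planned follow-up, and a condensed article may leave the window to the analysis plan. The missing window is thus not an error in itself. Multiple imputation is also planned, so patients lost to follow-up need not be counted as having no procedure.

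The NYHA point survives all of this. The test is named, reading NYHA at 12 months does not restore the ordering, and neither does dichotomising. The article does not say how many categories would be tested, so the 3 degrees of freedom are an inference.

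**Conclusion.** The point holds in limited form and is minor.

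- **NYHA class:** the named test wastes information. The cost is about 15 points of power, resting on one assumed class distribution, a common odds ratio and 10% loss. The article gives no NYHA rates, so the exact size is illustrative, but the direction is not in doubt when the effect is a shift along the scale.
- **PCI and CABG, randomised arms:** valid, with a small power loss. The weakness is interpretive: the proportion refers to no stated time.
- **PCI and CABG with registry patients (PET v CMR, or the advanced registry pooled against SPECT):** bias arises only if follow-up differs between groups and crude proportions are used. The article leaves both open. If both applied, a half-year difference in maximum follow-up would raise the false-positive rate to roughly 10% to 15% under the assumed rates.

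**What to change.** 1. Analyse 12-month NYHA class, and HF symptoms where graded, with a proportional-odds model that includes baseline NYHA as a prespecified covariate. Check the proportional-odds assumption, which is the price of the gain.
2. For PCI, CABG and either procedure, report time to first procedure as cumulative incidence, with a cause-specific Cox model for the group comparison. A fixed 12-month proportion is an acceptable simpler choice. This matters most wherever registry patients are included; there, define time zero for patients who are not randomised.
3. State in the PET v CMR section which methods its closing sentence refers to.

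The cost is mainly wording. Clinical data at baseline and 12 months are already scheduled. The article does not say that procedure dates are recorded, and the health-record query described under Subject evaluation does not list PCI or CABG. Chart review of resource use is planned and may supply the dates; the case report form should be checked before the time-to-event version is adopted.

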### Subject evaluation

At baseline, demographic and clinical data will be collected from all participants on standardized case report forms. These data will be collected from the most recent, routine history and physical examination that has been completed by the treating physician. Quality of life questionnaires (EuroQol and Minnesota Living with Heart Failure) will be administered. In addition, the above-mentioned laboratory samples will be collected. To address a secondary objective, whenever possible, an echocardiogram will be performed if LV ejection fraction has not been determined by echocardiography within 6 months prior to randomization. As much as possible, imaging procedures will be performed within 4 weeks after entry into the trial. Subsequent telephone follow-up and repeat blood work will be performed on a predetermined schedule (Table 2). If the patient cannot be reached by telephone for their final assessment, a query will be made at government or national health care resources to verify if any corresponding events have occurred since the last visit (search of corresponding codes for cardiac death, MI, cardiac arrest and cardiac re-hospitalization for WHF, ACS, or arrhythmia). A follow-up echocardiogram will be requested at one year (LV remodeling, LVEF). Within 3 months of the baseline scan the treating physician will be asked to record the HF management plan.

**Table 2 T2:** Patient assessment schedule

	**Baseline**	**3 months**	**6 months**	**12 months**	**18 months**	**24 months**	**36 months**	**48 months**
Imaging (SPECT, PET or CMR)	x							
Blood work	x			x				
Demographic and history	x							
Clinical data collected	x			x				
EuroQol questionnaire	x	x	x	x	x	x	x	x
MLWHF questionnaire	x	x	x	x	x	x	x	x
Telephone follow-up		x	x	x	x	x	x	x

*CMR* cardiac magnetic resonance, *MLWHF* Minnesota Living with Heart Failure, *PET* positron emission tomography, *SPECT* single photon emission computed tomography.

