#### Missing data

‘Missingness’ is considered to be missing at random (MAR) and mixed methods repeated measures (MMRM) and multiple imputation techniques will be used for handling missing data. In particular, for continuous outcomes at multiple time points MMRM will be used.

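### MLHFQ and EQ5D are given two unranked analyses, baseline adjustment depends on the data, and the missing-at-random assumption makes no exception for death

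*Protocol article*

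**What the plan says.** The Secondary outcomes section groups three continuous outcomes, LVEF, MLHFQ and EQ5D, under one rule: "analysis of variance will be used to compare trends over time between the advanced and standard technologies". It adds analysis of covariance only where relevant baseline differences turn up.

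The Missing data section gives a different rule. Missingness "is considered to be missing at random (MAR) and mixed methods repeated measures (MMRM) and multiple imputation techniques will be used", followed by "In particular, for continuous outcomes at multiple time points MMRM will be used". It does not name LVEF, and it does not except patients who have died.

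Table 2 schedules both questionnaires at baseline and at 3, 6, 12, 18, 24, 36 and 48 months. LVEF has one planned repeat (Subject evaluation): "A follow-up echocardiogram will be requested at one year". The Sample size section assumes uniform entry over 2.5 years, at least one year of follow-up and 10% loss per arm. The Analysis populations section makes intent-to-treat the main population for every objective except safety.

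**The concern.** MLHFQ and EQ5D are continuous and measured at several times, so both sentences apply to them. With incomplete data an ANOVA of trends and an MMRM can give different estimates, and nothing says which one counts.

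Three further matters depend on how this is settled:

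- If the ANOVA is the classical kind that needs every scheduled visit, it would rest on early enrollees, which fits poorly with an intent-to-treat main analysis.
- If covariate adjustment depends on baseline differences observed in the data, the model is chosen after looking, and precision available from the collected baseline value may be lost.
- If all missingness is MAR, quality of life after death is implicitly modelled from survivors, although cardiac death is part of the primary endpoint. An arm with more deaths would then not be marked down for them on these outcomes.

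**Working it through.** **1. Confirming the accrual inputs.** The plan's own randomized sample size (495 = 330 + 165) should follow from the accrual figures used below. Inputs from the Sample size section: one-year rates 30% v 40%, two-sided 0.05, power 80%, 2:1 allocation, accrual R = 2.5 years, minimum follow-up F = 1 year, 10% loss.

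- Hazards: λ1 = −ln 0.70 = 0.357 and λ0 = −ln 0.60 = 0.511, so the hazard ratio is 0.698.
- Event probability: P(λ) = 1 − [exp(−λF) − exp(−λ(R+F))]/(λR).
- Lachin–Foulkes: N = {z(α/2)·√[φ(λ̄)(1/Q1 + 1/Q0)] + z(β)·√[φ(λ1)/Q1 + φ(λ0)/Q0]}² / (λ1 − λ0)². Here φ(λ) = λ²/P(λ), Q1 = 2/3, Q0 = 1/3 and λ̄ is the weighted mean hazard.
- Result: N = 449 before loss and 449/0.90 = 499 after. With loss entered as a hazard of 10% per year, N = 496. Other formulas with division by 0.90 give 476 (Freedman) and 527 (Schoenfeld).

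The 495 is reproduced closely, so the accrual design is the one the plan used. No stated figure is disputed.

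**2. Who can reach each visit.** Under uniform entry, the share reaching month m before study closure is (R + F − m/12)/R = (3.5 − m/12)/2.5, bounded to 0–1. Maximum follow-up is 3.5 years, or 42 months.

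| Visit | Share | Of 330 + 165 |
|---|---|---|
| 3, 6, 12 months | 100% | 330 + 165 |
| 18 months | (3.5 − 1.5)/2.5 = 80% | 264 + 132 |
| 24 months | (3.5 − 2)/2.5 = 60% | 198 + 99 |
| 36 months | (3.5 − 3)/2.5 = 20% | 66 + 33 |
| 48 months | 0% (beyond 42 months) | 0 + 0 |

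These are ceilings before death or loss. A complete-data ANOVA would keep at most 66 + 33 = 99 of 495 patients through 36 months and none through 48.

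**3. Does a mixed model share that problem?** A simulation of 60 replicates used 495 patients, uniform entry, this visit schedule, no deaths and a true slope difference of −2. A random-slope mixed model gave −2.09 (Monte Carlo SE 0.08), so there was no detectable bias. This is as expected: visits lost to closure depend on entry date, not on outcome.

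**4. Always adjusting for baseline.** With equal variances and correlation ρ between baseline and follow-up, a change score has variance 2σ²(1 − ρ) and ANCOVA has σ²(1 − ρ²). The ratio is (1 + ρ)/2. At ρ = 0.5 it is 0.75 (25% lower); at ρ = 0.7 it is 0.85 (15% lower). The correlations are assumptions.

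**5. Death and MAR, as an illustration only.** The article gives no death rate for its arms. Assume 12-month mortality of 10% v 15% and mean EQ5D of 0.70 in survivors of both arms. Modelling the dead from survivors gives 0.70 − 0.70 = 0. Scoring death as 0 gives 0.70 × 0.90 − 0.70 × 0.85 = 0.630 − 0.595 = 0.035. At this utility each percentage point of mortality difference is worth 0.70 × 0.01 = 0.007, so equal mortality gives 0.

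**The case against.** The strongest reply is that the two sections fit together: Secondary outcomes names the arm-by-time comparison, and Missing data says how it is fitted when values are absent. The article condenses a fuller protocol, and detailed rules for death belong in an analysis plan that is not shown. That reading is reasonable, but the text does not make it, and both rules are stated as what will be done. The point about death is confined to the stated MAR assumption, which is too wide as written.

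Several stronger readings are not supported:

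- A reader might infer that MMRM also mishandles visits never reached. It does not, barring a secular trend; what remains is that a 48-month mean cannot be estimated on the planned accrual.
- A reader might infer that the plan will discard most patients. That happens only with classical complete-data ANOVA, which the article does not specify.
- A reader might say LVEF has no trend to analyse. Two time points still give a change to compare.
- A reader might carry the MAR problem into the QALYs. The Economic evaluation section draws utilities from EQ5D and MLHF but does not say that values imputed after death will be used.
- A reader might quote a 25–50% variance gain from baseline adjustment. That is relative to an unadjusted follow-up value (1 − ρ²), whereas the plan compares trends.

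The visit shares also rest on planned accrual. Trial status reports 249 patients, 20% of the total, in the second year of enrollment. A uniform 2.5-year pace would give 1/2.5 = 40% after one year and 2/2.5 = 80% after two. If accrual took 4 years (assumed, same minimum follow-up), the shares would be (5 − m/12)/4: 88% at 18 months, 75% at 24, 50% at 36 and 25% at 48. Complete data to 48 months would still be available for only a quarter.

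**Conclusion.** The point holds as a worthwhile improvement at little cost. It touches neither the primary analysis nor the sample size.

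Two methods stand unranked for MLHFQ and EQ5D; the conflict is direct for these two and not for LVEF. On the plan's own accrual, only MMRM can use the later questionnaire data sensibly. Baseline adjustment hangs on a data-dependent trigger when it could be fixed, for a variance gain over change scores of about 25% to 15% at assumed correlations of 0.5 to 0.7. MAR is declared for all missingness, which is the wrong assumption for values that do not exist after death. How much that last matter would move the EQ5D result cannot be known from the document: the 0.035 depends wholly on the assumed mortality gap, and the zero beside it is built in by assuming equal utility among survivors.

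**What to change.** In Secondary outcomes, replace the ANOVA sentence and the conditional ANCOVA sentence with:

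- **MLHFQ and EQ5D:** MMRM with baseline value, visit, arm and arm-by-visit, and one prespecified contrast at a visit every patient can reach by calendar, such as 12 months.
- **LVEF:** ANCOVA of the 12-month value with baseline LVEF as covariate.
- Baseline adjustment in all cases, whatever the observed balance.

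In Missing data, refer to the MMRM as that same main model and limit MAR to values missing while the patient is alive. An MMRM does not draw that distinction by itself, so say that imputation stops at the date of death. Report a while-alive estimate with a death-inclusive sensitivity analysis beside it, for example with EQ5D utility set to 0 after death.

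The cost is protocol and analysis-plan wording and a little more analysis; data collection is unchanged. The death-inclusive estimate mixes survival with quality of life, so it should not be shown alone.
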